### Sample size and power

#### Primary outcome

The primary outcome analysis will compare AYAHIV virologic suppression at 12 months post-intervention, between intervention versus control sites using generalized estimating equations with robust standard errors, providing unbiased marginal estimates of the intervention effect while adjusting for within-cluster correlations.

For the primary outcome, sample size estimates are based on the following assumptions: 2-sided superiority test with 90% power at *α* = 0.05, clinic sizes of 220 AYAHIV in active care per clinic (range, 113–590), levels of viral suppression < 50 copies/mL of 65% in control clinics (current data estimates this proportion at 48–68%), *ICC* = 0.05 (range, 0.04–0.08). Thus, we estimate that 12 clusters sampling at least 100 AYAHIV each on average will provide > 80% power to detect an absolute increase of 16% in virologic suppression in the intervention versus control clinics.

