#### Statistical analysis

Descriptive statistics will be presented with frequency (percent) or median (interquartile range) depending on the type and will provide overall and by allocation arm. Review of data distributions will be undertaken prior to applying any inferential statistics requiring specific assumptions and methods revised or corrective procedures undertaken. Covariates and specific details of analysis will be fully specified before database closure in a detailed SAP developed by the study statistician and study team. All statistical tests will be two-sided with nominal *α* = 0.05. Study endpoints are binary and will be approached in a similar way. The primary outcome analysis will compare AYAHIV virologic suppression at 12 months post-intervention implementation in intervention versus control sites using generalized estimating equations under a binomial model, with a log link and robust standard errors, providing unbiased marginal estimates of the intervention effect while adjusting for within-cluster correlations. Clustering will be by site using an exchangeable correlation structure. Estimates will be reported as risk ratios (RR) with robust 95% confidence intervals and *p*-values assessed at *α* = 0.05 for all comparisons. No additional adjustment variables will be included in the primary analysis. In subsidiary analyses, we will include covariate adjustment based on confounders selected a priori using direct acyclic graphs. Sensitivity analysis will address potential heterogeneity in clustering by evaluating endpoint models under different assumed correlation structures. Missing outcome data will be handled by complete case analysis in the first case and then by sensitivity analysis substituting alternate outcome values for missing data. Missing data in covariates will be handled by multiple imputations using chained equations. Analysis of secondary endpoints is not conditional on the outcome of the primary endpoint. Secondary endpoints will be approached identically as the primary endpoint. Planned subgroup analyses, which include by age group [10–14, 15–19, 20–24], sex, pregnancy status during the intervention period among females, duration of prior ART use, and ART regimen, will be carried out for primary and secondary outcomes using the same approach as the previously described. Exploratory analyses will include:

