#### Secondary outcomes

##### Adherence

Projected statistical power for comparing the secondary adherence outcomes between intervention versus control sites uses the same assumptions as above, thus having similar expectations around achieved power and minimal detectable differences.

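### At the protocol's own inputs the stated power of more than 80% is about 74% by normal approximation (about 65% on 10 between-clinic degrees of freedom), and the 90% in the same paragraph is out of reach

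*Protocol article*

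**What the plan says.** In the protocol article, under Sample size and power (Primary outcome), the assumptions open with a "2-sided superiority test with 90% power at" the 5% level. They continue with "levels of viral suppression < 50 copies/mL of 65% in control clinics" (the article adds "current data estimates this proportion at 48–68"%) and an ICC of 0.05 with a range of 0.04 to 0.08. The conclusion is that "12 clusters sampling at least 100 AYAHIV each on average will provide" more than 80% "power to detect an absolute increase of 16% in virologic suppression in the intervention versus control clinics".

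Three other places supply the rest of the design. Randomization and blinding gives 1:1 allocation, hence 6 clinics per arm. Participants and recruitment caps the post-intervention sample at 200 per site. Statistical analysis plans an unadjusted GEE with log link and robust standard errors, clustered by site, and states: "All statistical tests will be two-sided with nominal" alpha of 0.05.

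The Adherence paragraph prints no power figure of its own. It says that the projection "uses the same assumptions as above, thus having similar expectations around achieved power and minimal detectable differences".

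**The concern.** The paragraph carries two power levels, 90% as an assumption and more than 80% as the conclusion drawn from it, and does not reconcile them. Every input needed to check them is printed, so this is a question of arithmetic and not of detail deferred to an analysis plan.

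The figure concerns the primary endpoint. More than 80% power tells the reader that a true 16-point gain would be missed less than one time in five. If the real chance is nearer one in four, or one in three under a few-cluster reference distribution, a non-significant result would be weaker evidence against a 16-point effect than the protocol implies.

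**Working it through.** **Inputs** (all from the protocol article): k = 6 clinics per arm; m = 100 per clinic; control p0 = 0.65; intervention p1 = 0.65 + 0.16 = 0.81; ICC = 0.05; two-sided alpha = 0.05. Equal cluster sizes are assumed.

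**Attempt to reproduce the stated figure**

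- Design effect: 1 + (m − 1) × ICC = 1 + 99 × 0.05 = 5.95.
- Effective sample per arm: 600 / 5.95 = 100.8.
- Standard error of the difference: √[(0.65 × 0.35 + 0.81 × 0.19) / 100.8] = √(0.3814 / 100.8) = 0.0615.
- Standardised effect: 0.16 / 0.0615 = 2.60.
- Power, normal approximation: Φ(2.60 − 1.96) = **73.9%**.
- Power, noncentral t with 12 − 2 = 10 degrees of freedom: **65.1%**.

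Other forms of the calculation do not close the gap. The pooled-variance form gives 72.9% and the log risk ratio form 71.0% (normal). A finite-population correction for 100 sampled from 220 gives 77%. No two-sided version at the stated point values reached 80%.

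**Effect of the ICC range and of the sampling cap** (65% v 81%; normal / t on 10 df)

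| ICC | 100 per clinic | 200 per clinic |
|---|---|---|
| 0.04 | 81% / 73% | 85% / 77% |
| 0.05 | 74% / 65% | 77% / 69% |
| 0.08 | 57% / 48% | 59% / 50% |

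With 200 per clinic the design effect at ICC 0.05 is 1 + 199 × 0.05 = 10.95, so the effective sample rises only to 1200 / 10.95 = 109.6 per arm. With unlimited sampling it tends to 6 / 0.05 = 120 per arm, and power to 81% / 73%. At ICC 0.04 the limit is 6 / 0.04 = 150 per arm and 89% / 82%. So 90% is unreachable with 12 clinics at 65% control suppression anywhere in the stated ICC range.

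**Effect of the control rate** (ICC 0.05, 100 per clinic): 64% / 55% at 48% suppression, and 77% / 69% at 68%.

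**Detectable difference** from 65% (ICC 0.05, 100 per clinic): for 80% power, 17.1 points (normal) or 18.7 points (t); for 90% power, about 19.4 or 21.2 points.

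**Routes that do give more than 80%.** Each changes something the paragraph states:

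- ICC 0.04 in place of 0.05, normal approximation: 81%.
- A one-sided 5% test: 83% (normal).
- 200 per site and 68% control suppression at ICC 0.05: 80.6% (normal).
- 200 per site with a finite-population correction for 200 of 220, at 65% control suppression and ICC 0.05: 80.7% (normal).

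**Check on the planned type of test.** A simulation with 100 per clinic and ICC 0.05 gave 77% power for GEE with uncorrected robust standard errors and a z reference, with a type I error of about 9.8%. A cluster-level t-test in the same simulation gave 64.8%, with type I error near 5%.

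**The case against.** The strongest reply is that the t-based 65% is not the power of the planned analysis. The article plans a robust GEE and leaves the specifics to a SAP that is not shown; that SAP may well settle the small-sample handling. This stands, and it is why 74% is given first. A reader might infer that the trial's power simply is 65%. The documents do not support that: it is the power under one reasonable few-cluster reference. The point does not depend on it, because the normal approximation already falls short. The uncorrected robust test also misses 80%, at 77%, with a type I error well above 5%.

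A second reply is that 100 is a minimum and that favourable inputs within the stated ranges do reach 80%. This is also true. A reader might infer that the claim survives only at an ICC of 0.04, but that is too strong, since 200 per site with 68% control suppression gives 80.6% by normal approximation. These are departures from the printed base case, however, and the ranges also run the other way, to 57% / 48% at ICC 0.08.

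Third, a reader might infer that the adherence section contains a separate wrong figure. It does not; it only refers back to the primary calculation.

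Finally, the planned risk ratio with its 95% confidence interval would itself reveal imprecision, so a null result need not be misread. That softens the consequence but leaves the stated power wrong.

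**Conclusion.** The point holds. At the inputs printed in the protocol, power for a 16-point increase is about 74% by normal approximation, and about 65% on 10 between-clinic degrees of freedom, against a stated figure above 80%. The shortfall is at least 6 percentage points on the simplest method and about 15 with the few-cluster reference. The 90% cannot be reached at 65% control suppression within the stated ICC range, even at the 200-per-site maximum.

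These results rest on equal cluster sizes and the standard design effect; unequal clusters would lower power further. How the authors obtained their figure cannot be established from the article.

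**What to change.** Under Sample size and power, do one of two things:

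- restate the power for 65% v 81% with 12 clinics of 100 and ICC 0.05 as about 74% (normal approximation; about 65% with a t reference on 10 df); or
- restate the difference detectable with 80% power as about 17 points (normal) to 19 points (t).

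In either case, remove the 90% or explain how it relates to the conclusion. Show power at ICC 0.04, 0.05 and 0.08: 81%, 74% and 57% (normal); 73%, 65% and 48% (t). Have the Adherence paragraph refer to the corrected figure.

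The cost is a few lines of text and a less favourable stated power. No clinic, participant, outcome or procedure changes, and the primary model stays unadjusted as the protocol specifies.

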#### Secondary outcomes

##### Adherence

Projected statistical power for comparing the secondary adherence outcomes between intervention versus control sites uses the same assumptions as above, thus having similar expectations around achieved power and minimal detectable differences.

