## Background

HIV burden among adolescents and young adults (aged 10–24) worldwide is substantial, with an estimated 1.7 million adolescents aged 10–19 years living with HIV in 2019 and 460,000 adolescents and youth newly infected in the same year [1]. An estimated 85% of all adolescents and young people living with HIV (AYAHIV) reside in sub-Sharan Africa [SSA] [2]. This is concerning given that SSA has a young population, with 30–35% of the total population between 10 and 24 years of age [1]. While increased availability and access to antiretroviral therapy (ART) have significantly reduced pediatric mortality, healthcare workers (HCWs) face challenges in meeting the complex needs of the large number of surviving AYAHIV who must learn to manage HIV, a chronic, highly stigmatized, and transmittable illness. Furthermore, adolescents and young adults newly acquiring HIV in these developmental stages experience overlapping but distinct and equally complex needs that require tailored services.

AYAHIV in SSA face formidable health system, interpersonal- and individual-level barriers to retention in HIV care, uptake of ART, and achievement of viral suppression (VS) and worse outcomes compared to other age groups within HIV programs have been identified [3]. Results from the Population HIV Impact Assessments (PHIA) in four SSA countries, Zambia, Zimbabwe, Malawi, and Eswatini, demonstrated lower rates of HIV testing, ART uptake, and VS among 15–19-year-olds compared with adults [4]. Previous studies conducted in SSA have identified multiple factors impacting treatment outcomes in AYAHIV, many in common with adult populations but compounded by the challenges of adolescence and early adulthood, including psychosocial factors and lack of social support, as well as factors relating to health systems such as mistrust of HCWs and concerns about stigma and discrimination, especially when accessing sexual and reproductive health (SRH) services [5–11]. Evidence from our formative survey among 213 AYAHIV ages 10–19 years surveyed in Nampula Province Mozambique showed a high proportion of participants with missed ART doses and high levels of viremia, and over two-thirds self-reported challenges with ART adherence [12–14].

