#### Effectiveness outcomes

The primary outcome is viral suppression < 50 copies/mL at 12 months post-intervention implementation among AYAHIV at intervention and control sites, which will be assessed through real-time viral load testing.

Secondary outcomes include:

(1) ART adherence will be measured by using a validated Wilson self-report ART adherence measure administered on all AYAHIV participating in the one-time post-implementation assessment at 12 months post-intervention implementation [26, 27]. In addition, TDF levels will be measured on a subset of participants in care selected retrospectively in a case-control sub-study comparing AYAHIV who have VL < 50 copies/mL, versus those with VL ≥ 50 copies/mL. The Wilson measure has previously been implemented in this setting to assess ART adherence among AYAHIV during the first phase of the CombinADO study [12]. (2) Retention in care will be measured as objective evidence of engagement in the preceding 90 days among AYAHIV in care at intervention and control sites abstracted from routine clinic records.

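### The adherence power statement reuses the primary outcome's inputs, which cannot apply to TDF levels measured on a viral-load-selected subset and which no adherence figure supports for self-report

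*Protocol article*

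**What the plan says.** The adherence paragraph under Sample size and power gives no adherence proportion, ICC or sample size of its own. It says that power for comparing the adherence outcomes between arms "uses the same assumptions as above, thus having similar expectations around achieved power and minimal detectable differences".

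The assumptions it points to are in the Primary outcome paragraph: a "2-sided superiority test with 90% power at" α = 0.05, "levels of viral suppression < 50 copies/mL of 65% in control clinics" (the text adds that "current data estimates this proportion at 48–68"%), ICC 0.05 with a range of 0.04–0.08, and 12 clinics with at least 100 sampled in each on average. From these it states more than 80% power for an absolute gain of 16 points.

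There are two adherence measures. The abstract and Table 4 list both under the adherence outcome.
- The Wilson self-report is administered to everyone in the 12-month assessment.
- For the other, the Effectiveness outcomes section says that "TDF levels will be measured on a subset of participants in care selected retrospectively in a case-control sub-study", contrasting participants below and at or above 50 copies/mL.

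Two statements bear on the likely adherence level. The Background says that in the formative survey (213 participants aged 10–19) "over two-thirds self-reported challenges with ART adherence". The Effectiveness outcomes section says that "The Wilson measure has previously been implemented in this setting to assess ART adherence among AYAHIV during the first phase" of the project.

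**The concern.** The adherence paragraph asserts a property of the design. It is not a detail left for the analysis plan, so it can be tested against the rest of the protocol. Two inputs do not transfer.

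- **Sample.** A subset is smaller than the full sample, and this one is selected on the primary outcome. Neither the sample per clinic nor the clinic-population proportion carries over to TDF levels.
- **Control proportion.** The 65% is a viral suppression level. The retention paragraph gives retention its own control level (50–60%), but adherence gets none, although the Wilson measure had already been used in this setting.

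Table 4 presents adherence as a mediator of the effect on suppression. A null result on self-report or TDF would be read against a level of power that the design does not have, and might be taken as evidence against the mechanism.

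**Working it through.** **Inputs.** From the protocol: 6 clinics per arm (12 clinics, 1:1), m = 100 per clinic, ICC 0.05, control level 65%, gain 16 points, two-sided α = 0.05. Assumed, because the protocol gives no figure: adherence control levels of 25–50%, and TDF subsets of 10–50 per clinic.

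**Formulas.** Design effect DE = 1 + (m − 1) × ICC. SE² = [p0(1 − p0) + p1(1 − p1)] × DE / (6m). Normal power = Φ(|p1 − p0|/SE − 1.96). The t version uses a noncentral t with 2 × (6 − 1) = 10 df, to allow for only 12 clinics.

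**1. The figure being carried over.** DE = 1 + 99 × 0.05 = 5.95, so the effective n is 600/5.95 = 100.8 per arm. SE² = (0.65 × 0.35 + 0.81 × 0.19)/100.8 = 0.3814/100.8, so SE = 0.0615 and 0.16/0.0615 = 2.60. Power is 74% (normal) or 65% (t). Pooled-variance, arcsine, log risk ratio and logit versions give 71–73%. At 200 per clinic it is 77% (normal). More than 80% is reached at ICC 0.04 (81%) or with a one-sided test (82%), but the protocol says "All statistical tests will be two-sided with nominal" α = 0.05. At ICC 0.08 power is 57%.

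**2. Self-report, full sample.** m = 100, ICC 0.05, gain 16 points:

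| Control level | Power, normal | Power, t (10 df) | Detectable at 80% power, normal | Detectable at 80% power, t |
|---|---|---|---|---|
| 65% | 74% | 65% | 17.1 points | 18.7 points |
| 50% | 65% | 56% | 19.0 | 20.9 |
| 40% | 63% | 55% | 19.4 | 21.4 |
| 33% | 65% | 56% | 19.1 | 21.2 |
| 25% | 69% | 60% | 18.4 | 20.4 |

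For 33%: SE² = (0.33 × 0.67 + 0.49 × 0.51)/100.8 = 0.4710/100.8, so SE = 0.068 and the ratio is 2.34. Over the protocol's ICC range of 0.04–0.08, normal power at 33% runs from 73% down to 48%.

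**3. TDF subset.** 65% v 81%, ICC 0.05:

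| Per clinic (assumed) | DE | Effective n per arm | Power, normal | Detectable at 80% power, normal |
|---|---|---|---|---|
| 10 | 1.45 | 41.4 | 38% | 24.7 points |
| 20 | 1.95 | 61.5 | 53% | 21.1 |
| 30 | 2.45 | 73.5 | 60% | 19.6 |
| 50 | 3.45 | 87.0 | 68% | 18.2 |

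**4. Selection on viral load.** As an illustration only, assume that 90% of suppressed and 30% of unsuppressed participants are adherent, and that suppression is 65% v 81%.
- Full population: 0.65 × 0.9 + 0.35 × 0.3 = 69.0% v 0.81 × 0.9 + 0.19 × 0.3 = 78.6%, a difference of 9.6 points.
- Equal numbers of suppressed and unsuppressed drawn across both arms together: the suppressed share becomes (0.65/1.46)/(0.65/1.46 + 0.35/0.54) = 40.7% in control and, likewise, 61.2% in intervention. Adherence is then 54.4% v 66.7%, a difference of 12.3 points.
- Equal numbers drawn within each arm: 0.5 × 0.9 + 0.5 × 0.3 = 60% in both arms, a difference of zero.

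The unweighted arm difference thus depends on how the subset is drawn.

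**The case against.** **The formative data.** A reader might infer that the formative survey contradicts 65%. It does not. Reporting challenges with adherence is neither a Wilson score nor a proportion non-adherent, the survey covered ages 10–19 and the trial 10–24, and control clinics will have 12 months of optimized care, including pill boxes and staff training. The survey casts doubt on 65%, but the 33% above is an assumption. This part of the objection stands.

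**The right comparator for self-report.** The paragraph claims similarity to the primary outcome. On like-for-like inputs the loss is from 74% to about 65%, some 9 points. That lies within the 64–77% (normal) implied for the primary outcome by the protocol's own 48–68% control range, and the sample is the same. So setting 65% power against the stated 80% and blaming the whole gap on adherence would be wrong. This also stands.

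**Whether TDF is covered at all.** The Populations for analyses section speaks of one adherence outcome with the primary's population, which fits the Wilson measure. The TDF contrast is described by viral load, not by arm. The plural in the adherence paragraph proves little, since the retention paragraph also uses a plural for a single endpoint. The subset size is not given, and sampling weights could be set in the analysis plan. These points show that the paragraph may have been meant for self-report only. They do not rescue it as written: the abstract and Table 4 place TDF levels within the adherence efficacy outcome, and the Statistical analysis section has secondary endpoints analysed in the same way as the primary.

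**Conclusion.** The concern holds in limited form.

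- **TDF levels.** The reused assumptions cannot apply. Power of about 38–68% rests on an assumed 10–50 per clinic and would rise with a larger subset. The selection problem would remain at any subset size unless the analysis is weighted.
- **Self-report.** The 65% is unsupported, not refuted. At ICC 0.05 and 100 per clinic, power for a 16-point gain is about 74% (normal) or 65% (t) at 65%, and 63–69% or 55–60% at assumed levels of 25–50%. The difference detectable at 80% power moves from about 17 to about 19 points (normal). Calling this similar to the primary outcome is optimistic, not impossible.
- **The inherited figure.** More than 80% is not delivered at any of these levels at ICC 0.05, but part of that shortfall comes from the primary outcome paragraph and is not specific to adherence.

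The absence of a subset size or an adherence threshold from the article is not counted as an error.

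**What to change.** Limit the adherence power statement to the self-reported measure. Recompute power and detectable difference from the proportion adherent on the Wilson measure in the first phase, and show a range of proportions and ICCs (at least the protocol's 0.04–0.08).

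State that no between-arm power is claimed for TDF levels. Alternatively, give it separately for the planned subset size, with an arm comparison weighted for the sampling on viral load.

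The cost is a few sentences and a short calculation; the sponsor's first phase used the Wilson measure, so the proportion should be at hand. No extra participants are needed and no analysis of the primary outcome changes. The stated figure is likely to become less favourable.

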##### Retention

Projected statistical power for the comparison between arms for the secondary retention outcomes between intervention versus control sites assumes clinic “in care” population sizes of an average of 220 AYAHIV in active care (12-month period) for a total analysis size = 2640 across 12 sites and an assumed proportion retained in care (90-day window) of 50–60% under control conditions.

